## 6.2 Exclusion criteria

Patients will be excluded if they one or more of the following:

- are under 35 years old
- are 80 years old or older
- are not eligible for CVD risk assessment.

### 6.3 Recruitment

The PHOs will invite practices to join the study. Interested practices will be visited and twenty practices who agree to be part of the study will be randomised. The eligible population will be identified automatically and anonymously through an existing CVD population register held by the PHOs and PREDICT. Notices informing patients about the study will be placed in GP waiting rooms of practices who have been allocated to the POC group and an Information Sheet will be available (Appendix 2).

### 6.4 Study groups

- **POC group:**

The 10 practices randomised to the POC group will receive the following materials and training in their use from Roche Diagnostics.

**Table 3 Cobas b 101 device and consumables**

| Material name
(Product name)       | Material Number | Unit       |
|---------------------------------------|-----------------|------------|
| Cobas b101                            | 06378668190     | each       |
| HbA1c disc                            | 06378676190     | Box of 10  |
| HbA1c control                         | 06380204190     | 2 vials    |
| Lipid panel disc                      | 06380115190     | Box of 10  |
| Lipid panel control                   | 06380182190     | 2 vials    |
| 5 x Safe-T-Pro Plus
Lancing device | 03603539200     | Box of 200 |

- **Laboratory group:**

The 10 practices randomized to the laboratory group will continue current practice of requesting laboratory testing to complete CVD risk assessment.

### 6.5 Randomisation

Participating practices will be randomised by the biostatistician into POC and laboratory groups. Randomisation will be stratified by practice size (number of effective FTE GPs where 0.8 FTE = 1.0 effective FTE: <2 effective FTE small, ≥2 effective FTE large)) and rurality of location (urban [within the Whangarei city boundary] or rural). As these factors are potentially associated, directly or indirectly, with the probability of CVD risk assessment completion; stratification will ensure a balance in these potential confounders between the two study arms.

### 6.6 Blinding

This is a single blind trial. Whilst it is not possible to blind practices to having the Cobas b 101 or not, study academic investigators will analyse the CVD risk assessment endpoint data blinded to the practice allocation to POC or laboratory group. This data will be collected through the PREDICT CVD risk assessment programme as part of routine clinical practice. Study staff will have no influence or involvement in patient clinical data collection or recording. The PREDICT data will be provided to the investigators by practice separated into two groups. At the end of the analysis the allocation assignment to POC or laboratory group will be revealed to the investigators.

## 6.7 Withdrawal criteria

Patients will receive CVD risk assessment as part of normal clinical care which includes testing for lipids and diabetes. For patients in the POC group, a laboratory test may be requested by the health care practitioner or participant, instead of, or in addition to, point-of-care testing. This will not withdraw the patient from the study.

## 6.8 Primary outcome measure

- Completed CVD risk assessment at end of study.

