## **Study period**

Expected duration 3-6 months (dependent on practices' rate of risk assessment).

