## 5. Study Objectives

Primary study objective:

To evaluate the impact of POC testing for lipids (TC/HDL) and diabetes (HbA1c) on the frequency of completed CVD risk assessments in the eligible population. The primary aim of this study is to determine whether POC testing for lipids (TC/HDL) and diabetes (HbA1c) is at least as effective as the control (laboratory) on the frequency of completed cardiovascular disease (CVD) risk assessments in the eligible population at 12 months in primary care practice.

Secondary study objective(s):

1. To evaluate the impact of POC testing for TC/HDL and HbA1c on the frequency of incomplete ("parked") CVD risk assessments in the eligible population.
2. To evaluate the impact of POC testing for TC/HDL and HbA1c on CVD risk assessments in the eligible population by age, sex, deprivation quintile, for Māori and non Māori, diabetes, smoking status, and previous CVD risk score.
3. To evaluate the impact of POC testing for TC/HDL and HbA1c on the average duration of CVD risk assessment.
4. To evaluate whether the impact of POC testing is the same in urban areas (e.g. Whangarei City) as in rural areas and in large and small GP practices.
5. To conduct a cost analysis of POC testing compared with laboratory testing.
6. To evaluate the acceptability, feasibility and practice impact of POC testing for TC/HDL and HbA1c in general practice.

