## 6.11 Practice follow-up

Each of the ten practices allocated to the POC group will undergo a training session in the use of the Cobas b 101 device. About half way through the study e.g. at 3 months, and at the end of the study practices will be contacted by PHO facilitators to document any additional staff time and/or other resources required by the use of the Cobas b 101 device and to assess its overall acceptability, feasibility and practice impact. The study will be continued until at least 1000 risk assessment have been performed and all the point of care consumables have been utilised by the POC group. It is estimated therefore the study duration will be in the order of 3-6 months.

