Our updated sample size calculations are based on analyses estimating the number of eligible people who are eligible for first risk assessment and those that will require a follow-up CVD risk assessment (for example those over 15% CVD risk, and people with diabetes are recommended for annual screening). Within a 12 month period (Aug 2012-2013) it appeared that about 30% of the eligible population had a CVD risk assessment. We assume a primary event rate of 30% in the laboratory group and a 10% increase to 40% in the POC group. This figure is based on a study set in community pharmacies where POC testing for cholesterol risk management led to a 10% increase. The non-inferiority margin is set at 5%. Taking into account an intraclass correlation coefficient of 0.025 as suggested by Elley et al (2005) from three New Zealand CRCTs; a 0.025 one-sided level of significance and study power of 90%, we estimate a minimum sample size of 940 risk assessments (470 in each group) and 10 practices per group is needed assuming an average of 50 patients per practice. Therefore, the sample size is similar to the previous power calculations.

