### 7.2.2 *Study effects*

Generalized estimating equations (GEE) or random effects mixed models will be used in treatment evaluations, adjusting for the effect of clustering within practices and important baseline prognostic factors (e.g. practice location (urban/rural), size (number of GPs). Analysis of the non-inferiority hypothesis for the primary outcome will be evaluated by observing whether the lower limit of a one-sided 97.5% CI (or equivalently a two-sided 95% CI) is above the non-inferiority limit of -5%. In the case that non-inferiority is evident, assessment as to whether POC is superior to the control will be carried out using the same approach but comparing to a zero difference. A per-protocol analysis will also be performed in order to check the robustness of the results. Time series analysis will be conducted to describe changes in patterns of use of the POC device, for example increased use initially followed by a decline to a steady state level. Sensitivity analyses for the rate of CVD risk assessment will then be calculated for the latter period as being more indicative of ongoing community use of the POC device.

Duration of CVD risk assessment will be calculated from the start of the population of the PREDICT CVD risk assessment template to completion, i.e. when the five year CVD risk value is calculated.

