### Key milestones

| Date           | Milestone                                                                                   |
|----------------|---------------------------------------------------------------------------------------------|
| May 2013       | Ethics submitted                                                                            |
| June 2013      | Ethics approval                                                                             |
| July 2013      | Recruit practices                                                                           |
| August 2013    | Start of study                                                                              |
| August 2013    | Study halted due to manufacturing problems cobas b 1010 discs                               |
| May 2014       | Study recommenced after re-validation cobas discs, retraining practices and Ethics approval |
| June 2015      | Estimated end of study                                                                      |
| September 2015 | Analysis complete.                                                                          |
| November 2015  | Paper submitted.                                                                            |

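### The primary outcome has no single time point: the aim says 12 months, other sections say 3-6 months or a supply-driven end of study, and the sample size fits 12 months only

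*Protocol*

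**What the plan says.** The Protocol describes the window of the primary outcome in several ways.

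- Overview (Objectives) and section 5: the primary aim concerns completed "risk assessments in the eligible population at 12 months in primary care practice".
- Overview (Primary outcome) and section 6.8: "Completed CVD risk assessment at end of study". Section 7.1 speaks of completion during the study.
- Overview, Study period: "Expected duration 3-6 months".
- Section 6.11: the study continues until at least 1000 assessments are done and the POC group has used all its consumables. It then adds: "It is estimated therefore the study duration will be in the order of 3-6 months".
- Appendix 5, Key milestones: the study restarts in May 2014, and the "Estimated end of study" is June 2015. The timeline chart in the same appendix ends follow-up in Q1 2015.

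The planning rate has an explicit window: "Within a 12 month period (Aug 2012-2013) it appeared that about 30% of the eligible population had a CVD risk assessment" (7.1). The calculation then proceeds: "We assume a primary event rate of 30% in the laboratory group and a 10% increase to 40% in the POC group". The margin of 5 points comes next and becomes the decision rule in 7.2.2, where the lower confidence limit must be one that "is above the non-inferiority limit of -5" percent. Neither place gives the margin a time base.

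**The concern.** The outcome is the proportion of an eligible list, drawn at week 0, that has a completed assessment by the cut-off. That proportion grows with time, so the estimand is not defined until the window is. The current text offers 12 months, 3-6 months, about 13 months, and an end that depends partly on how fast one arm uses its supplies. The start is open too: the milestones list a start and a halt in August 2013 and a restart in May 2014, while the chart shows follow-up from Q4 2013.

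At stake is the link between the outcome and the decision rule. The sample size rests on a 12-month control rate. A fixed absolute margin applied at a shorter window tolerates a larger relative loss of completed assessments, and the planned power no longer applies. With a cut-off tied to POC supplies, the horizon is also not fixed in advance independently of what happens in one arm.

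**Working it through.** **Step 1. Reproduce the plan's figure.** Inputs from 7.1: 30% v 40%, margin 5 points, one-sided 0.025, power 90%, ICC 0.025, 50 patients per practice.

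- n = [0.30×0.70 + 0.40×0.60] × (1.960 + 1.282)² / (0.10 + 0.05)² = 210.1, so 211 per arm
- design effect = 1 + 49 × 0.025 = 2.225
- 211 × 2.225 = 469.5, so 470 per arm and 940 in total

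This matches the Protocol exactly. The 470 therefore rests on 30% v 40%, and the 30% is a 12-month figure.

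**Step 2. Move the window.** The Protocol gives no accrual pattern. I assume either a constant hazard, p(m) = 1 − (1 − p₁₂)^(m/12), or linear accrual, p(m) = p₁₂ × m/12, in each arm, with p₁₂ of 30% and 40%. The effective size is 470/2.225 = 211.2 per arm.

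- SE = √[(pL(1−pL) + pP(1−pP))/211.2], where L is laboratory and P is POC
- P(claim) = Φ((pP − pL + 0.05)/SE − 1.96)

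Example, 6 months, constant hazard: pL = 0.1633 and pP = 0.2254, so SE = 0.0384. Then (0.0621 + 0.05)/0.0384 − 1.96 = 0.96, which gives 83%.

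In each cell the constant-hazard result comes first and the linear result second.

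| Window | Laboratory rate | POC rate as planned | 5 points as share of laboratory rate | Power for non-inferiority |
|---|---|---|---|---|
| 3 months | 8.5% / 7.5% | 12.0% / 10.0% | 59% / 67% | 82% / 78% |
| 6 months | 16.3% / 15.0% | 22.5% / 20.0% | 31% / 33% | 83% / 77% |
| 11 months | 27.9% / 27.5% | 37.4% / 36.7% | 18% / 18% | 89% / 88% |
| 12 months | 30% | 40% | 17% | 90% |
| 13 months | 32.1% / 32.5% | 42.5% / 43.3% | 16% / 15% | 91% / 92% |

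**Step 3. What a fixed absolute margin lets through.** Take a POC arm that would sit exactly at the margin at 12 months (25% v 30%) and apply the same formulas. The true difference is −2.9 / −2.5 points at 6 months and −1.6 / −1.25 points at 3 months. The chance of claiming non-inferiority is 2.5% at 12 months, 9-11% at 6 months and 26-33% at 3 months. At 11-13 months it is 2-3%.

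**Step 4. Type I error under the stated hypothesis.** At a true difference of −5 points the numerator is zero, so P(claim) = Φ(−1.96) = 2.5% whatever the window.

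**Step 5. The supply rule.** The supplies table in section 10.1 lists 198 boxes of 10 discs of each type, which is 1,980. The plan of 50 assessments in each of 10 POC practices is 500. If 500 took 3-6 months and discs went only to patients, 1,980 would take 1,980/500 = 3.96 times as long, about 12-24 months. The 3-6 month estimate therefore does not follow from the rule that it is said to follow from.

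**The case against.** The strongest reply is that the short window is not a live prospect. This version is dated 30 March 2015, about 10 months after the restart, so 3-6 months had already passed and appears to be text that was not updated. The current milestones fall close to the 12-month aim, and step 5 suggests that the supply rule pushes the end later, not earlier. This stands. It limits the numerical consequence but does not supply a time point: the duration text and the supply-based rule are still in force, and the chart and the milestones disagree within one appendix.

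A reader might infer that a shorter window makes non-inferiority far too easy to claim, or inflates the type I error. The documents do not support that. The margin is an absolute 5 points, so the true differences of about −1 to −3 points in step 3 lie inside it, and a claim there is correct under the stated hypothesis. Those percentages become errors only if the margin is read as proportional, which the Protocol never says. A shorter window also lowers the power for the planned gain.

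A reader might also take the 40% and the margin to be stated as 12-month figures. Only the 30% is. The 10-point gain comes from a community pharmacy study with no window given, and the margin's link to 12 months is inferred from its place in the calculation.

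Finally, the accrual patterns are assumptions. Section 7.2.2 itself raises the possibility that POC use rises first and then settles, which neither pattern describes.

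**Conclusion.** The point holds as a contradiction in current text about the primary outcome. The Protocol does not say at which time completion is counted, and its sample size supports a 12-month window only. By inference, so does its margin.

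The size depends on which window is used. At the present milestones (about 11 months if the restart is paired with the end of the chart, about 13 if paired with the June 2015 date) the margin is 15-18% of the control rate and power is 88-92%, close to plan. At the 3-6 months still written in two places, the margin would be 31-67% of the control rate and power about 77-83%. These figures assume constant-hazard or linear accrual and the Protocol's ICC and cluster size. The contradiction itself needs no assumption, and it cannot be left to an analysis plan because the Protocol states the conflicting windows itself.

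**What to change.** - In the Overview (objectives and primary outcome), section 5, section 6.8 and section 7.1, define the primary outcome as a completed assessment within 12 months of one stated restart date. Use the same calendar window in both arms and cut the PREDICT data there for all 20 practices.
- Remove or correct the 3-6 month duration in the Overview and section 6.11.
- State in 6.11 that the consumables rule does not set the outcome cut-off.
- Align the chart and the milestones in Appendix 5 with that window.
- State in 7.1 and 7.2.2 that the 30% rate and the 5-point margin refer to it.

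The cost is a protocol amendment, which section 13.2 sends to the Ethics Committee. Because it changes how 6.11 works, the team should also check whether that section's renewed verbal consent from practices applies. No extra data collection is needed: PREDICT captures assessments automatically, and the milestones already run past 12 months from the restart. About one month of late completions would leave the primary count and could be reported descriptively.

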## 6.9 Secondary outcome measures

- Incomplete (“parked”) CVD risk assessment at end of study.
- Completed CVD risk assessment by age, gender, Māori/non Māori, diabetes, smoking status, deprivation quintile, practice location (urban/rural), practice size, , previous CVD risk score.
- Average duration of CVD risk assessment.
- Cost analysis.
- Acceptability, feasibility and practice impact of POC testing for CVD risk assessment in general practice.

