### 3.3 Assessment of cholesterol and diabetes

As part of a CVD risk assessment, the New Zealand guidelines recommend blood lipid testing and use of the ratio of total cholesterol to high density lipoprotein (TC/HDL, fasting or non-fasting) in the risk calculation. In 2009, screening for diabetes was also recommended as part of the risk assessment using either fasting glucose or haemoglobin type A1c (HbA1c, fasting or non-fasting).

Currently, if the lipid and diabetes values are not known at the visit, the GP or practice nurse must order a blood test (via a laboratory referral form). Transmission from the screen to the PREDICT server will not occur unless all the data fields are filled in. If screening blood tests are not available the assessment can be "parked" and saved until all data is subsequently available. Ideally then a risk assessment would be completed with the patient on a second visit. It is not known what proportion of risk assessments remain incomplete due to the laboratory testing step and necessity for two consultations.

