### 3.4 Point-of-care testing for cholesterol and HbA1c

A new point-of-care (POC) device (Cobas b 101 developed by Roche Diagnostics) that can perform both TC/HDL and HbA1c tests has recently become available on the New Zealand and global markets. It is estimated that a thirty minute consultation could provide a completed CVD risk assessment (see figure below and Appendix 3). This includes 15 minutes to undertake the finger prick sampling and provide the test results. The Cobas b 101 practitioner to complete the risk assessment and provide tailored advice in the one consultation.

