## 6. Study Design

This is a pragmatic, prospective, open, blinded endpoint, cluster randomised controlled non-inferiority trial in primary care.

The study setting is the patients enrolled in GP practices within the Northland region of New Zealand that belong to either Manaia Health Primary Healthcare Organization (PHO) or Te Tai Tokerau PHO. Manaia Health has 24 practices and Te Tai Tokerau has 15. A cluster randomised controlled trial is proposed within twenty of these general practices who use PREDICT and agree to participate in the study.

The eligible population is comprised of patients enrolled in these practices who are aged between 35-79 years, who as determined by their GP, meet age, sex and ethnicity guideline criteria for CVD risk assessment (Table1) and do not have a previous recorded CVD risk assessment or if they have had a previous CVD risk assessment are overdue for their next check (Table 2). All CVD risk assessment data will be automatically captured within the PREDICT server before, during, and after the study as part of usual clinical practice.

The unit of randomisation will be the practice and data collection will be at the individual patient level. The study involves random allocation of the practices to either the POC group (Cobas b 101) or laboratory (control) group. A cluster RCT design was necessary because the cobas b 101 device will be provided to the practice as a cluster level intervention.

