## 7. Statistical Considerations

### 7.1 Sample size

The study will involve a two-arm parallel cluster randomised controlled trial (CRCT) design with 20 practices (10 practices per arm). The primary outcome is whether the eligible patients have had a completed CVD risk assessment during the study. Preliminary analyses indicated that at least 70% of the enrolled populations within Manaia and Te Tai Tokerau PHOs have had a completed CVD risk assessment since 2006. Many of these people will be due for repeat CVD risk assessment. Significant delays to the conduct of this trial have occurred both prior to commencement and having to halt the trial due to manufacturing problems of the HbA1c discs. During this time practices have accelerated their CVD risk assessments in order to meet the national target (by July 2014 that 90% of the eligible population have had a CVD risk assessment in the previous 5 years.) As at April 2014, the two PHOs have screened approximately 80% of their eligible enrolled populations over the last five years. Therefore this trial now needs to adopt **a priori a non-inferiority hypothesis**.

Our previous sample size calculations May 2013, were as follows; We assumed a primary event rate of 70% in the laboratory group and a 10-15% increase to 85% in the POC group. This figure is based on a study set in community pharmacies where POC testing for cholesterol risk management led to a 10% increase. Taking into account an intraclass correlation coefficient of 0.025 as suggested by Elley et al (2005) from three New Zealand CRCTs; a 5% two-sided level of significant test and study power of 90%, we estimate a minimum sample size of 1000 risk assessments is needed (on average 50 patients per practice).

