### 7.2.5 *Procedures to account for missing data*

PREDICT data submitted to the Enigma server is required to be complete in order to get a CVD risk assessment response (CVD risk score and ability to go to Your Heart Forecast). However, it is possible to view incomplete templates. Only those templates where laboratory values are missing (i.e. all other variables are entered) will be counted as “parked” CVD risk assessments.

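### The parked outcome is read once, at end of study, with no minimum template age, so laboratory-arm assessments still awaiting results are counted with abandoned ones

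*Protocol*

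**What the plan says.** The parked outcome in section 6.9 is status at a single date: an incomplete "CVD risk assessment at end of study". The follow-up table in section 6.12 places the collection of risk assessment data only at end of study, and section 6.12.2 has the investigators receive completed or parked status then. Section 7.2.5 gives the counting rule: "Only those templates where laboratory values are missing (i.e. all other variables are entered) will be counted as" parked. The rule has no minimum time since opening, and no last-opening date or run-out period is given.

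The two pathways differ in timing. On the laboratory route (section 3.3), when values are not known at the visit, the template is parked until they arrive: "Ideally then a risk assessment would be completed with the patient on a second visit". For POC testing (section 3.4), "It is estimated that a thirty minute consultation could provide a completed CVD risk assessment".

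The primary outcome carries similar wording in section 6.8, "Completed CVD risk assessment at end of study", but section 7.1 makes it cumulative: "whether the eligible patients have had a completed CVD risk assessment during the study".

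**The concern.** Section 4 explains why incomplete assessments matter: patients given a blood test form often never go to the laboratory. Section 3.3 adds that the share of assessments left incomplete for this reason is unknown. The parked outcome is the trial's measure of that loss.

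A snapshot without an age rule cannot separate loss from ordinary turnaround. If every laboratory-arm patient eventually had the blood taken and the assessment completed, the arm would still show a pool of parked templates at the cut, made up of those opened most recently. The POC arm would show a much smaller pool. The parked comparison could then favour POC even if no assessment was lost at the laboratory step.

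**Working it through.** **The plan's own figure.** The sample size in section 7.1 reproduces and is not in dispute. With 30% against 40%, a 5-point margin, one-sided 0.025 and 90% power, n = (1.960 + 1.282)² × (0.30×0.70 + 0.40×0.60) / (0.10 + 0.05)² = 210.1, or 211 per arm. The design effect is 1 + 49 × 0.025 = 2.225, and 211 × 2.225 = 469.5, which rounds up to the stated 470 per group.

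**Inputs for the pending pool**
- Study length T: 12 months in section 5, and 3-6 months in sections 1 and 6.11. The milestones in Appendix 5 run from May 2014 to June 2015, about 13 months.
- Laboratory-arm assessment rate: about 30% of eligible patients in 12 months (section 7.1).
- Mean lag L from opening to completion: not given. Assumed to be 1, 2 or 4 weeks.

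**Formula.** If templates are opened at a steady rate r per week, about r × L are waiting at the cut, out of r × T opened. The share labelled parked with no true loss is L/T.

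| L (weeks) | T = 52 weeks | T = 26 weeks |
|---|---|---|
| 1 | 1/52 = 1.9% | 1/26 = 3.8% |
| 2 | 2/52 = 3.8% | 2/26 = 7.7% |
| 4 | 4/52 = 7.7% | 4/26 = 15.4% |

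For 500 laboratory-arm templates (10 practices of 50), that is about 10, 19 or 38 over 12 months, and 19, 38 or 77 over 6 months.

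**Why these are upper bounds for each lag.** The formula lets every laboratory-arm assessment wait. Section 3.2 says available results are filled in automatically, and section 3.3 requires a test only when values are unknown. If, say, half the assessments needed no new test, the 4-week figure over 12 months would be 0.5 × 7.7% = 3.8%. The difference between arms is smaller again, because section 6.7 lets POC practices order laboratory tests.

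**Carry-in at the start.** Both arms used laboratory testing before the study, so both inherit parked templates. Mainly the laboratory arm leaves a fresh pool at the end, so carry-in does not cancel the effect on the parked outcome.

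**Primary outcome.** In points of the eligible population, the pending pool is at most 30% × L/52 = 0.6, 1.2 or 2.3 for 1, 2 or 4 weeks. This is not a loss from the laboratory arm's completed count. At a steady rate that arm completes the pool it inherited and leaves a similar one behind. The 30% also comes from completions in an ordinary 12-month window, so it already contains that turnover. The gap between arms arises because POC practices leave less unfinished at the same date.

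**The case against.** The strongest objection is that a reader might infer bias in the primary non-inferiority test, since 2.3 points is not small beside a 5-point margin. The documents do not support that reading. The primary outcome is cumulative (section 7.1), laboratory completions are largely replenished from the inherited pool, and finishing sooner is part of what the device is meant to achieve (sections 3.4 and 4). To call the whole end-of-study gap bias would be to choose a different estimand. This objection stands and limits the point to the secondary outcome.

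A reader might also infer that every laboratory assessment, and no POC assessment, is affected. Sections 3.2, 3.3 and 6.7 rule that out. The effect is differential, not exclusive to one arm.

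The size is open to challenge because the lag is assumed. The larger shares need the 3-6 month duration, while the current milestones imply about 13 months. This stands, so the 12-month column is the more relevant one.

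It can also be said that cut-off and run-out rules belong in the statistical analysis plan, which is not shown, and that turnaround is measured separately as duration (section 7.2.2). The analysis plan could indeed add such a rule. But section 7.2.5 does more than leave the matter open: it states which templates count, and that rule includes those merely waiting. The duration outcome ends when the risk value is calculated, so it does not show which uncompleted templates were waiting and which were lost.

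Finally, opening a template happens after randomisation, and POC testing may change who has one opened. This caution stands and bears on the choice of denominator.

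**Conclusion.** The parked outcome, as sections 6.9 and 7.2.5 fix it, mixes normal laboratory turnaround with assessments lost at the laboratory step. The direction is towards POC and follows from the protocol's own description of the two pathways. The size depends on a lag the protocol does not give. With steady openings and mean lags of 1 to 4 weeks, at most about 2% to 8% of laboratory-arm templates over 12 months would be labelled parked with no true loss, and about twice that over 6 months.

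For the primary outcome, the corresponding end-of-study difference of about 0.6 to 2.3 points is an upper bound and partly a real effect of faster completion. It justifies a sensitivity analysis, not a change of definition and not a claim that the non-inferiority test is invalid.

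**What to change.** In section 7.2.5, count a template as parked only if it still lacks laboratory values a fixed time after opening, with the same interval in both arms. Limit the outcome to templates opened at least that long before the data cut. Keep the eligible population as denominator, as secondary objective 1 has it, so that the act of opening a template does not define the comparison. Fix the interval before the arms are compared.

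This needs no later extract, because template start times are already required for the duration outcome. The cost is that templates opened in the last weeks drop out of this secondary outcome.

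The alternative is a short run-out, which is feasible because "All CVD risk assessment data will be automatically captured within the PREDICT server before, during, and after the study". It would have to be short: 90 days after a June 2015 end falls in September 2015, when Appendix 5 has the analysis complete.

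Leave the primary outcome as cumulative completion during the study. Add one sensitivity analysis that credits completions within the same fixed interval for templates opened in the study window. Crediting completions for late-opened templates does need the run-out. Without it, apply the analysis to templates opened at least that interval before the cut. The sample size does not change.
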